## Methods/design

### Study design

This study is a randomised controlled trial conducted in a large university hospital centre in France.

The psycho-social intervention lasts 12 months. It simultaneously targets healthcare teams, department management and SC management. The randomisation was therefore performed at SC level.

The quantitative study of the effects of the intervention combines an assessment via self-administered questionnaire and the collection of clinical indicators in the course of a mandatory medical check-up in the occupational medicine department in the CHU. Three assessment times are planned: a baseline assessment, an assessment immediately after the intervention and an assessment 1 year after the end of the intervention (Fig. 1).

**Fig. 1 Fig1:**
[figure not shown]
CHRYSALIDE Flowchart

### Objectives

To assess the impact at one and 2 years of a standardised psychosocial intervention programme on the structural empowerment score in an “intervention SC”, in comparison with a “control SC”.To assess the impact of the intervention at one and 2 years on psychological empowerment scores.To detail the effects of the intervention on sub-dimensions of structural and psychological empowerment.To assess the effect of the intervention on motivational processes and factors.To assess the effect of the intervention on managerial practices.To assess the impact of the intervention on working conditions, health and performance.

### Sub-centers recruitment

The targeted CHU comprises 12 SCs with five to six departments each, each in turn grouping a number of care units for a total of 20 to 25 per SC. The size of the SCs varies from 800 to more than 1000 salaried staff. The hierarchical structure is presented in Fig. 2.

**Fig. 2 Fig2:**
[figure not shown]
Hierarchical structure of the CHU

The recruitment of SCs before randomisation was conducted in collaboration with CHU-level management according to the following eligibility criteria:
At the CHU management level, agreement by the CHU General Director (*Directeur Général*, DG), the human resources director, the president of the medical community and the general nursing coordinator.No major reorganisation or re-affectation planned over the study period.At the SC management level, agreement by the SC top-manager, the senior chief nursing officer, the senior chief medical officer and the chief nursing officer.Both medical and surgical activity in the SC.

A first random selection was performed among the eligible SCs to determine the two SCs to be included in the study. The randomisation is performed by the scientific committee, which is coordinated by the principal investigator. It comprises the researchers associated with the project (co-authors of this paper).

All the departments in the two SCs were assumed to be included, given the agreement obtained by SC senior management on the strength of its hierarchical responsibility. The SC senior chief medical officer is in charge of information to heads of department, and the SC chief nursing officer is responsible for information to front-line managers.

### Data collection and randomisation

The data collection is conducted by two clinical research nurses, two occupational physicists and two psychologist trainees. They are managed by a clinical study coordinator. Staff members are specially recruited for this data collection. Their sole supervisor is the study’s principal investigator.

The quantitative indicators are collected at the time of the mandatory check-up in the occupational medicine department in compliance with French law. This check-up is yearly and thus fits the planned data collections in the study.

After information to front-line managers, all the professionals working in the departments in the two SCs are called on to attend the medical check-up. This call takes the form of an internal letter signed by the head of the occupational medicine department, inviting the person to contact the secretariat to make an appointment. In case on non-response by the agent, two telephone reminders can be made by the secretariat.

The consultations are planned over a period of 3 months at most. The professionals are first seen by a clinical research nurse who presents the research protocol and proceeds to inclusion in the study on the following criteria:
any professional working in healthcare departments, whatever their profession (chief medical officer, doctor, front-line manager, nurse, nursing assistant, technical staff, secretariat etc)written agreement by the professional to take part in the quantitative research.

In case of refusal to participate, the professional is taken to a waiting room until he/she sees the occupational physician for the regulatory, non-standardised check-up.

Professionals agreeing to participate are asked to wait around 40 min in the waiting room and during this time to complete a questionnaire on a tablet. The questionnaire enables the collection of psychometric indicators. The participant is then called by the doctor for a check-up lasting around 35 min. The doctor follows a standardised layout and codes the clinical indicators retrieved from the interview and the clinical examination on a computer. At the end of the consultation the doctor can address the person to an occupational nurse for any complementary biological tests required.

Following the inclusion campaign and baseline data collection, a second random selection is performed by the scientific committee to determine which of the two SCs is the “intervention SC” and which serves as the control.

The collection of indicators at 1 year and 2 years is performed in the same manner.

### The procedure in the intervention group

#### General logic of the intervention

The process we propose concerns the whole system and involves from the outset a transfer of power in the form of a W-QoL negotiation for each unit. Thus, by way of a W-QoL operation coherent with HAS recommendations, all the protagonists from management to healthcare teams directly experiment on an original space for dialogue and co-construction, which supposes 1) for the teams, an increase in scope for action, 2) for the department heads and front-line managers endeavouring to implement a supportive and participative management style and 3) for CHU and SC-level management an arbitration between interests and structural support for teams, without intermediaries.

To facilitate the encounter and to moderate resistance relating to classic roles and relationships, the overall procedure is accompanied for each department by a facilitator (social psychologist or sociologist) following a purpose-designed standardised protocol that was pre-tested in the course of a pilot phase in five CHU units in 2015 and 2016. The facilitators are under the responsibility of the principal investigator and benefit from the supervision of the scientific committee.

We hypothesise that this “experience-generating” procedure on a large scale, agreed to by the senior management and secured and mediated by the scientific protocol is liable to change representations and practices among all the protagonists, for greater empowerment of the medical care teams.

#### Main stages in the intervention

Step 0. Preparation of the intervention: In the 12 months following confirmation of funding: presentation and validation of the procedure with 1) the CHU General Director, and other directors from the CHU-level management, and 2) the senior management of SCs complying with the inclusion criteria, and finally 3) with the Unions. Creation of the steering committee composed of the directors from the CHU-level management and including the principal investigator and the head of the occupational health department. Invitation to the steering committee to visit an innovating business enterprise recognised in France for its system of piloting based on collective field intelligence. This phase ends with the randomisation and the collection of baseline indicators from the occupational medicine departments. Aim: Top-management acculturation to empowerment, implication of the senior management from the CHU and all the SCs liable to be selected in the random draw, considered as experimentally controlled factors and critical prerequisites for the success of implementation [18].Step 1. Start of the intervention: integration of the senior management from the intervention SC into the steering committee and Training seminar n° 1. The seminar intended for department and unit-level management and the senior management of the “intervention SC”, also involving the CHU-level management. This takes place over a half-day, introduced by the DG, the SC senior chief medical officer and SC chief nursing officer, followed by the presentation of the protocol and training on pro-empowerment management. The training includes 1) theoretical contributions on empowerment and management practices, and 2) the intervention of the Chief Executive Officer (CEO) of an enterprise recognised in France for its pro-empowerment management and its level of performance. This CEO shares his personal experience in the transition to empowerment, and then mediates a workshop debate on these practices with the investigator. All the participants are then invited to pursue the exchanges in a friendly manner on the occasion of a buffet. Aim: acculturation and mobilisation of the whole hierarchy for the intervention, promoting the adoption of empowerment practices in the experimental arm.Step 2. Qualitative diagnostic phase implicating the various departments and lasting several months. The facilitators meet the department and unit-level managers. They present the system of accompaniment of the healthcare teams. They then carry out exploratory interviews with professionals over a period of two to 3 months. This is followed by the drafting of a qualitative report for each department, covering the resources and constraints perceived by the teams. This written report should not contain any recommendations, so that any proposal for improvement derives from the teams in an empowerment logic. The reports are then validated by the scientific committee. Aims: to facilitate an alliance between facilitators and the front-line management, the department head and the team, and to foster their implication.Step 3. Feed-back phase on the reports to the hierarchy, lasting 1 month. The facilitators and the scientific committee hand in all the reports to the steering committee for validation. This is followed by feedback to the department and unit management. Aims: to offer management advice and prepare for the accompaniment of teams with managers at all levels.Step 4. Training seminar n°2 intended for management at department level and the management in the “intervention SC”, also involving CHU-level management. As for the first seminar 5 months previously, the event is introduced by the DG, the senior head doctor in the SC and the chief nursing officer. The investigator presents a detailed account of the team accompaniment measures as provided for in the protocol, and the recommended managerial practices. There are new outside contributors, one CEO and one of his staff, belonging to an innovating enterprise recognised in France for its pro-empowerment management and performances. The two contributors present their respective experiences of the same participatory process, and then together mediate a workshop and debate alongside the investigator on the accompaniment and management practices to be instated. All the participants are then invited to pursue the exchanges in friendly manner around a buffet. Aim: to mobilise the whole hierarchical chain towards pro-empowerment management for the implementation of step 5.Step 5. Feedback, collective debate on the reports and presentation of the accompaniment plan in each unit, totalling 20 to 23 feedback contributions for the “intervention SC”, over a period of 1 month. The meeting gathers all the healthcare team, the unit-level manager, the head of department, the SC-level managers, the CHU human resource director. After a round-table and presentation of the plan, the facilitator reads out each section of the qualitative analysis, and submits each to validation by the team via collective debate. He/she mediates the debate among protagonists, fostering the emergence of solutions. Finally, he/she proposes a collective accompaniment plan in local working groups in collaboration with management. Aims: to convince of the reality of the negotiation process and implicate the teams in the system aiming to promote empowerment.Step 6. Finalisation, launching and accompaniment of the W-QoL working groups in each department, over a period of 3 months. In a post-feedback meeting, the groups are formed by the healthcare teams freely with respect to their composition (number, professions) and their objectives. Working groups or research groups already in existence are integrated into the process. The groups comprise two reference persons – one medical, one paramedical (nurse or nursing assistant), with the back-up of the unit and department management. The head of the department and the unit manager support the reference persons and the groups, and oversee the mutualisation of developments across the different groups, and the overall synthesis in a department perspective. The facilitator has the job of mobilising and supporting the reference persons and the groups, while at the same time providing personalised accompaniment and managerial advice for the head of the department and the unit manager. Once a month, the SC chief nursing officer holds a meeting jointly with the investigator and the front-line managers of the intervention SC on the theme of managerial practices. Aim: in concomitant manner, to foster 1) implication and structural and psychological empowerment in the teams, and 2) the adoption of pro-empowerment managerial practices by department and unit-level managerial staff and SC management.Step 7. Negotiation and co-construction meetings in each unit, over a period of 1 month. As for the feedback phase, the meeting assembles the healthcare team, the head nurse, the department head, the SC manager, the human resource manager. The themes broached in this discussion are defined by the working groups in a bottom-up logic. They are made available upstream of the encounter by the investigator to the CHU and SC-level management in the course of a preparatory steering committee meeting. The meetings: Following a round-table, the working group reference persons present the improvements established by the working groups and express any demands for support requiring structural provisions. The CHU and SC-level managerial staff valorise implication and innovations, take an active part in collective reflection on improvements, arbitrate on the scope available to the management, while at the same time informing on the challenges to be dealt with at the overall facility level. The head of the department and the unit manager are encouraged to outline the terms of the meeting and to mediate the exchanges, with the help of the facilitator. Aims: concomitantly to favour 1) implication and psychological and structural empowerment in the teams, 2) the transfer of facilitating functions to unit management and department heads, these being considered as one aspect of pro-empowerment management, and 3) at CHU and SC level, managerial practices that take account of the collective intelligence of the field.Step 8. Structural adjustment phase, lasting 2 months. Following the meetings, the managerial bodies implement the decisions and proposals they have made, taking care to comply with undertakings and/or to communicate with the teams in case of unexpected developments. The actions of the management bodies are coordinated in the course of a steering committee meeting gathering the SC managers, the CHU human resource director, the investigator and the facilitators. The SC-level managers are encouraged to return in person to the teams. The facilitators prepare for the cessation of their activities and encourage the department and unit managers to maintain the working groups and their reference persons. Department and unit managers organise team events to take leave of the facilitators, review the accompaniment provided and discuss perspectives for the future. Aims: the start of an improvement loop combining 1) pro-empowerment management in the departments, 2) CHU and SC managerial piloting of performance via negotiation and discussion, and 3) structural and psychological empowerment and team implication.

### The control SC

The “control SC” is merely subject to the annual occupational medicine follow-up, providing the measures at T0, T1 and T2. The participants in the quantitative study carried out at the time of the check-ups are in no way informed of the randomisation to come or the future accompaniment of one of the two SCs. This system makes it possible to dissociate the mandatory health follow-up by occupational medicine from the quantitative study that is common to the two SCs on the one hand, and the collective intervention specific to the “intervention SC” on the other. Thus all participants undertake to be followed up in the long term independently from any intervention.

During the intervention period in the “intervention SC”, the “control SC” functions in the normal manner for the CHU, according to the usual decision-making provisions.

### Criteria for discontinuing intervention

At the individual level, the professionals are free to participate in the intervention. They can therefore decide for themselves to remain outside of the accompaniment. At the unit and department level, the intervention can be interrupted if the head of the department objects to the accompaniment. These complaints are handled by the scientific committee in collaboration with the steering committee.

It should be noted that the two committees each have the power to interrupt intervention in a unit.

### Outcomes

The intervention aims to improve both the structural empowerment and the psychological empowerment of individuals. However, to determine the efficacy of the intervention, and also to understand any effects as accurately as possible, it appears worthwhile assessing conceptual network of empowerment in more global manner [44], here envisaged as predictors and outcomes of empowerment. These are listed in Table 1.

**Table 1 Tab1:** Key outcomes of the CHRYSALIDE study

Domain	Outcomes *(subdimensions)*	Instruments
Empowerment	Structural empowerment *(opportunity, support, information, resources)*	CWEQII, self-reported questionnaire [45]
	Psychological empowerment *(meaning, autonomy, skills, impact)*	PES, self-reported questionnaire [21]
Motivational processes	Basic psychological needs *(autonomy, competence, social affiliation)*	W-BNS, self-reported questionnaire [46, 47]
	Motivation *(intrinsic, identified, introjected, external motivations, lack of motivation)*	MWMS, self-reported questionnaire [48]
	Affective commitment	ACNC, self-reported questionnaire [49]
Working conditions	Empowering leadership *(delegation of authority, accountability, coaching for self-direction, information-sharing, skill development, coaching for innovation)*	LEBQ, self-reported questionnaire [50]
	Authentic leadership *(transparency, ethics, balanced processing, awareness)*	ALQ, self-reported questionnaire [51]
	Social support *(coworkers, supervisor, and institutional support)*	SPOS, self-reported questionnaire [52, 53]
	Distributive justice *(workload, salary, benefits, responsibilities)*	Organizational justice self-reported scale [54, 55]
	Global justice	Overall justice scale [56, 57]
	Work enrichment and design *(autonomy, feedback, significance, identity, variety of tasks)*	WDQF, self-reported questionnaire [58, 59]
	Role stressors *(role ambiguity, role conflicts)*	RCAS, self-reported questionnaire [60, 61]
	Illegitimate tasks *(unreasonable tasks, unnecessary tasks)*	BITS, self-reported questionnaire [62, 63]
	Quantitative workload	QWI, self-reported questionnaire [64]
	Satisfaction with work schedule	Adapted from usual satisfaction Likert scales [65, 66]
	Legal compliance of the work schedule	Institutional indicator collected by CHU
	Physical exertion at work	Borg 15 points Scale, assessment by practicioner [67]
	Bio-mechanical constraints *(gestures and postures, patient handling activities, activities prior to or following direct patient handling)*	Questionnaire created by the French group of Musculoskeletal Disorders, assessment by practicioner [67, 68]
Health status	Job satisfaction	Likert scale, Self-reported [65]
	Well-being *(pleasure, displeasure, arousal)*	JAWS, Self-reported questionnaire [69]
	Stress	PSS-4 [70, 71]
	Emotional exhaustion	MBI-GS [72]
	Depression	SDI, Diagnosis by practitioner [73]
	Body measurements *(Waist-to-hip ratio, BMI)*	standardized medical assessment
	Heart function *(blood pressure, heart rate)*	standardized medical assessment
	Medical history *(diabetes, high blood pressure, coronary artery disease)*	standardized medical assessment
	Dependent relative at home	standardized medical assessment
	Present medications *(psychotropic, analgesic, diabetes, cholesterol-lowering, antihypertensive treatments)*	standardized medical assessment
	Tobacco consumption	standardized medical assessment
	Alcohol consumption	standardized medical assessment
	Sleep disorders	standardized medical assessment
	Musculoskeletal disorders *(neck, shoulder, elbow, wrist, lumbar)*	standardized medical assessment
	Somatoform disorders	standardized medical assessment
Performance	Absenteeism	Institutional indicator collected by CHU
	Quality of care in the unit	Single-item indicator, self-reported [74]
	Safety of care in the unit	HSOPSc, self-reported questionnaire [75]
	Personal performance at work	HPQ, self-reported questionnaire [76]
	Unit performance	Institutional indicator collected by CHU
	Unit adverse events	Institutional indicator collected by CHU

Psychological empowerment covers cognitions that reflect complex and dynamic motivational processes at work among individuals [12, 15], in terms of 1) internalisation or externalisation of the locus of causality of behaviours in the workplace and 2) actual professional commitment [77]. These processes are also assessed.

Beyond concepts to be measured, the type of measure can entail advantages and drawbacks, for instance depending on whether a questionnaire is self-administered or hetero-administered by a doctor. Likewise, recourse to a standardised medical questionnaire can enable a more reliable evaluation of certain aspects of working conditions, such as biomechanical constraints, and it can diagnose certain health conditions.

### Sample size

Our estimate is based on the effect observed by Dahinten (2014) on the overall score for structural empowerment. Given the hierarchical structure of the data in the present study, (“professional” level nested in the ‘“functional unit” level, in turn nested in the “department” level) an inflation factor needs to be applied to the standard calculation of sample size [78]. The calculation of the inflation factor is based on the following hypotheses:
an intra-class Correlation Coefficient (ICC) equal to 0.001 (within-SC correlation) We did not find any estimation in the literature of an ICC corresponding to our main judgement criterion and our study population. However ICC values are classically around 0.001 to 0.1 [79]an alpha risk of 5%a statistical power of 80%a difference of 0.12 points between global structural empowerment scores for professionals in the intervention group between T1 and T2 [42]a standard deviation of the global structural empowerment score of 0.56 points [42]

With these hypotheses, the number of professionals to include per group is 519. In all, 1038 professionals should be included. This expected number is close to the overall numbers of professionals in the two SCs. Given the considerable risk of loss to follow-up, the choice was to aim for an exhaustive coverage of the two SC, i.e. 600 to 700 individuals per group. We also rely on the compulsory nature of the check-up to reach this objective.

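### The stated 80% power with 519 per group rests on an unsupported ICC of 0.001, the bottom of the plan's own range, applied to one cluster per arm; above an SC-level ICC of about 0.003 no number of staff reaches 80%

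*Protocol article*

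**What the plan says.** The protocol article randomises at SC level (Study design), and a second draw decides which of the two selected SCs receives the intervention (Data collection and randomisation). There is therefore one SC per arm.

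The Sample size section says that an inflation factor is needed because professionals are nested in functional units and units in departments. Its inputs are:

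- "an intra-class Correlation Coefficient (ICC) equal to 0.001 (within-SC correlation");
- "an alpha risk of 5"% and "a statistical power of 80"%;
- "a difference of 0.12 points between global structural empowerment scores for professionals in the intervention group between T1 and T2";
- "a standard deviation of the global structural empowerment score of 0.56 points".

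On the ICC it states: "We did not find any estimation in the literature of an ICC corresponding to our main judgement criterion and our study population". It then adds: "However ICC values are classically around 0.001 to 0.1". The conclusion is: "With these hypotheses, the number of professionals to include per group is 519", or 1038 in all. Recruitment aims for 600 to 700 per group because of expected loss to follow-up. No other ICC value is examined.

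The Statistical analysis section plans a mixed linear model with SC as a fixed effect and department or unit as a random effect, adjusted for the T0 score and other covariates. It also plans to estimate the ICC for department or unit.

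**The concern.** The ICC dominates a calculation with very large clusters. Here the value used is the lowest in the range the authors quote, no reason is given for it, and the result is an unqualified 80%. With a whole SC as the cluster, small changes in the ICC change the answer greatly.

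The section also justifies the inflation by one structure (units within departments) and labels the ICC with another (SC), while the planned model uses the first. The stated power may then describe neither the plausible range of clustering nor the analysis that will be run. A reader weighing a non-significant result would have only the 80% figure to go by, in a trial whose results are intended to inform public policy and replication elsewhere.

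**Working it through.** **Inputs** (Sample size section): difference d = 0.12, SD s = 0.56, alpha 5%, power 80%, ICC ρ = 0.001. Sidedness is not stated; two-sided reproduces the figure. I take 0.12 as the difference between groups, which also reproduces it. SCs have 5 to 6 departments and 20 to 25 units (Sub-centers recruitment).

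**Step 1: reproduce 519.** Without clustering:

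n0 = 2 × (1.96 + 0.8416)² × 0.56² / 0.12² = 341.9 per group.

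With the whole SC as one cluster, n = n0 × [1 + (n − 1)ρ]. Solving for n:

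n = n0(1 − ρ)/(1 − n0ρ) = 341.9 × 0.999/(1 − 0.3419) = 518.9, i.e. 519.

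Clusters of 20 to 200 people at ICC 0.001 give only 348 to 410. So 519 comes from one cluster per arm.

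**Step 2: the ceiling.** The effective sample size per arm is n/[1 + (n − 1)ρ], which tends to 1/ρ as n grows. Reaching 80% needs an effective 341.9 per arm, so ρ must be below 1/341.9 = 0.0029.

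**Step 3: power with the SC as cluster.** SE = √(2s²[1 + (n − 1)ρ]/n) and power = Φ(d/SE − 1.96). For example, at n = 519 and ρ = 0.01 the design effect is 1 + 518 × 0.01 = 6.18, SE = √(0.6272 × 6.18/519) = 0.0864, and power = Φ(1.389 − 1.96) = 28.4%. The difference detectable with 80% power is 2.8016 × SE.

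| SC-level ICC | 519 per SC | 600 | 700 | Limit, any n | Detectable difference at 519 |
|---|---|---|---|---|---|
| 0.001 | 80.0% | 83.5% | 86.8% | 99.8% | 0.12 |
| 0.002 | 67.7% | 70.7% | 73.5% | 92.3% | 0.14 |
| 0.003 | 57.9% | 60.2% | 62.5% | 79.0% | 0.16 |
| 0.01 | 28.4% | 28.9% | 29.4% | 32.8% | 0.24 |
| 0.05 | 9.8% | 9.8% | 9.8% | 10.0% | 0.51 |
| 0.1 | 6.9% | 6.9% | 6.9% | 6.9% | 0.71 |

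The formula counts the upper rejection tail only; counting both gives 7.6% in the last row.

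**Step 4: clustering at the levels the model uses.** With k clusters per SC, m = 519/k people per cluster, design effect 1 + (m − 1)ρ, a noncentral t with 2k − 2 degrees of freedom, and no baseline adjustment:

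| Clustering only at | Power at 519, ICC 0.01 | Power at 519, ICC 0.1 |
|---|---|---|
| Department (5-6 per SC) | 57-63% | 15-17% |
| Unit (20-25 per SC) | 85-87% | 44-50% |

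Example: with 20 units, m = 25.95, design effect 1.25, SE = 0.0389, d/SE = 3.09, 38 degrees of freedom, power 85%. At 600 to 700 per SC the unit-level figures at ICC 0.01 are 89-94%.

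**Step 5: baseline adjustment.** The documents give no T0-T2 correlation. If it is assumed to be 0.5, 0.6 or 0.7, and the ICC applies to the adjusted residual, n0 falls by a factor (1 − r²) to 256.4, 218.8 or 174.3. The SC-level ceiling then moves to 0.0039, 0.0046 or 0.0057.

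**The case against.** The strongest reply has four parts.

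*The calculation is correct and the assumption is disclosed.* Both are true. The ICC is listed among hypotheses, and the lack of an estimate and the wider range are printed beside it. A reader might infer an arithmetic error; there is none. Disclosure does not give a reason for the lowest value, and the 80% that follows carries no qualification.

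*The range is not tied to SC level.* This stands. The section does not say to what kind of cluster 0.001 to 0.1 applies. Both SCs belong to one hospital under common management, and both had to have medical and surgical activity, so a small between-SC ICC is not implausible. A reader might infer that the trial is known to be underpowered. The documents do not show that; they show that the claim depends on a value nobody has estimated.

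*Power is better if clustering sits at unit level.* This stands too. A reader might infer that 80% fails over nearly the whole range whatever the structure. That holds only for SC-level clustering: unit-only clustering keeps power above 80% at ICC 0.01. It does not do so at 0.1, and 519 was not derived that way.

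*More staff and T0 adjustment help.* They do. It would be wrong to say that extra staff stop helping above the ceiling: at ICC 0.003, going from 519 to 700 raises power from 57.9% to 62.5%. They cannot bring it to 80%. Adjustment moves the ceiling only to about 0.004-0.006 under the assumed correlations.

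**Conclusion.** The point holds as a problem with a sample-size assumption. The stated 80% is right at an SC-level ICC of 0.001 and falls quickly above it: to 58% at 0.003, 28% at 0.01 and about 7% at 0.1 with 519 per SC. Under the plan's own calculation (SC as cluster, SD 0.56, no gain from adjustment) no sample size gives 80% above about 0.0029. These SC-level figures treat the between-SC variance as known. With one SC per arm the trial cannot estimate it, so they are if anything optimistic.

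Separately, the inflation factor contains neither the unit nor the department level that the section cites and the planned model includes. The stated power therefore does not describe the planned analysis, for which it could be higher or lower depending on where clustering lies and how large it is.

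A reader might go further and infer that a null result will be misread as evidence of no effect. The documents do not say how a null result would be interpreted, so that remains a risk and not a finding.

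**What to change.** - Replace the unqualified 80% with a table of power and detectable difference at 600 to 700 per SC, for ICC 0.001, 0.003, 0.01, 0.05 and 0.1, shown separately for SC-, department- and unit-level clustering. State any T0-T2 correlation used.
- State that 80% at SC level, on the present calculation, requires an ICC below about 0.003.
- Use the T0 data to estimate the department and unit ICCs, and restate the detectable difference for the planned mixed model before T2 data are analysed.
- State that these estimates cannot supply the SC-level ICC, which cannot be usefully estimated with one SC per arm and remains an assumption.
- Do not add participants; more staff cannot overcome the SC-level ceiling.

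The cost is one rewritten paragraph and one variance-component analysis of baseline data. The design and the planned model do not change. The stated power becomes less favourable.
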